### Intervention

We have designed two educational interventions:

Intervention A: written information.

We will give written information about inhalation techniques to the patient. We will design a leaflet about the correct inhalation techniques containing the main devices the patients use in our area. We will include four devices: Handihaler, Turbuhaler, Accuhaler and pMDI. We will describe all the steps necessary to perform the correct technique including images to illustrate the most relevant ones.

The patients included in this group will be asked how they use their inhalers and the interviewer will write down the mistakes in a template designed to follow the SEPAR guidelines [1]. When the inhalation techniques have been performed, the interviewer will give the leaflet to the patients and will invite them to read it and to identify differences between the steps of the correct inhalation technique (leaflet) and the technique they have performed.

In the follow-up visits we will ask the patients about the leaflet and about the differences they have found.

Intervention B: written information about inhalation techniques plus instructor training.

We will give written information about the inhalation technique to the patient (leaflet described above) and we will train the patient about correct inhalation techniques. The training of instructors in the use of inhaler devices has been carried out at the Pediatrics Neumology Service of Hospital Materno Infantil (Málaga). We will perform training in three steps:

Patients will be asked how they use their inhalers. Using a variety of placebo inhalers, all of them will demonstrate, to the instructor, how they use their inhalers.

When the patient has given the demonstration, the trainer will ask about the problems and perceived mistakes with the technique.

The trainer will demonstrate the proper technique. Each device will be used and its technique will be explained step by step. The importance of following the correct technique every time the patient uses the inhaler device will be emphasized.

Finally, the patients can ask questions and they will practice the techniques until they are correct or until the patient becomes tired.

In the follow-up visits we will review the inhalation technique and we will correct any mistakes or clear up any doubts as explained previously. The objective here is for the patients to identify their mistakes, and if they cannot, to remind them of the proper technique by giving as many demonstrations as necessary.

### Recruitment

Patients will be contacted using their health center records. They will be invited to participate in the study after a brief explanation by telephone about the research aims and they will receive an appointment in the health center. At this first appointment (inclusion visit) patients will receive more detailed information about the study and, if they agree to participate, they will sign the written consent.

At this point, subjects will be asked whether they have a preference for one of the interventions and they will be divided into two groups (Figure 1). Those who select the preference group choose their intervention and they will form two arms of the study. The participants without a preference will join the randomized group and they will be randomly allocated into the three arms of this group.

In the preferences group, the two arms correspond to the two educational interventions designed for this study. In the randomized group the three arms will be: intervention A, intervention B and a control arm.

The randomization will be made using the block randomization technique. The blocks consist of six patients, two subjects per group or three patients, one patient per group (Intervention A, Intervention B and control). The blocks will be marked with a number from 1 to 96 and they will be chosen at random to create the allocation sequence using a sequence of random numbers generated by the Microsoft Excel 2003 program with the function fx:RAND(). The assignment to this group will be made by contacting the person responsible for random sequence by phone. Because the patients are from various health centers, the randomization and the presence of the two interventions and control subjects in all the health centers will be guaranteed.

After randomization all the study data will be recorded and the performance of correct inhalation techniques will be measured in all groups (inclusion visit). In the case of the control group, the inhalation techniques will be tested asking them about how they use their inhalers and the interviewer will write down the mistakes in the template designed. The interviewer will only correct the critical mistakes. In the follow-up visits the subjects will be invited to perform the inhalation technique and the mistakes will be written down.

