## Background

Drugs for inhalation are the cornerstone of therapy in obstructive lung disease. Inhalers are the principle vehicles for the effective administration of medication. They allow high lung deposition of the drug and minimize systemic adverse drug reactions [1,2]. The effectiveness of drugs for inhalation can be influenced by many factors including age, sex, education of the patient, duration of disease, type of inhaler used, correct inhalation technique and use of several inhalers [2,3].

There are three main categories of inhalers: pressurized metered dose inhalers (pMDIs), dry powder inhalers (DPIs) and small volume nebulizers (SVNs). DPIs and pMDIs are the devices most commonly used for drug delivery in the treatment of asthma and COPD patients [1,2].

Technical features of inhaler devices have improved over time. However, the effectiveness in delivering drugs to the lung depends on correctly performed inhalation maneuvers. Incorrect usage of inhalers is a significant problem for both asthma and COPD management because it may result in diminished therapeutic effects, resulting in poor control of symptoms and thereby insufficient disease management [4-6]. As a result, patients might receive treatment, but without proper education and training in correct inhalation techniques, the therapeutic benefit is less than optimal [2].

In a previous study, we observed that up to 75 % of patients do not perform a correct inhalation technique (data not published) and other studies show a similar percentage of error [7-9]. Many inhalers are complicated to use and some require up to eight steps [1].

Efficient use of pMDIs requires coordination between simultaneous inhalation and device actuation, a slow and continuous inspiratory flow rate during inhalation followed by a breath hold of at least ten seconds. Patients frequently fail to exhale fully before inhalation, they activate the device before or at the end of inhalation, or while breath-holding. Other common errors are high inspiratory flows, not shaking the device before use and stopping inspiration when the spray collides with the throat. Other drawbacks of these devices are that they contain environmentally unfriendly propellants and most of them provide no dose counter, so the patients do not know the number of doses remaining and they use the device when it is empty [1,9,10].

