The use of DPIs removes the coordination problem; however mistakes in the inhalation techniques are high. The most common errors are: not placing the device correctly, exhaling into the mouthpiece, low inspiratory flows and incorrect breath-holding. The most critical mistakes may be exhalation into the mouthpiece and low inspiratory flow, because the humidity and inadequate flow reduce the amount of drug released and its ability to reach the lungs [1,10].

Other factors associated with improper use of devices in patients with COPD are related to age and cognitive status [11,12], the number of devices [10,13] and the training of healthcare professionals. Healthcare personnel responsible for teaching the correct use of inhalation devices are lacking in basic knowledge and user skills [10,14]. To acquire the skills for using these devices, health professionals and patients must be adequately educated and trained [15,16].

The inability of patients to use their inhaler device correctly may be a direct consequence of insufficient or poor inhaler technique instruction. The quality of the initial instruction is of paramount importance for the outcome of inhalation therapy. Written instruction alone is insufficient in teaching correct inhalation techniques. Verbal instruction and technique assessment and reassessment are essential for patients to achieve a proper technique [17]. Patients who receive inhalation instructions at least once more after the initial instruction have better inhalation techniques compared with those who only receive instruction at the time of prescription [18]. Training in correct inhaler use rather than instructor demonstration appears to be important [19,20].

The objective of this study is to test the efficacy of two educational interventions to improve inhalation techniques in patients with COPD.

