### Sample size

This was calculated to detect a correct inhalation technique percentage difference between groups of 25 %, with a statistical power of 80 % and a confidence level of 95 %, assuming a percentage of expected losses of 40 %. The final sample size is 495 patients with COPD who meet the selection criteria mentioned above. In the Randomized group it will be necessary to include 297 patients, and in the Preferences group 198 (99 patients per arm).

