### Statistical analysis

A descriptive statistical analysis will be performed for all the study variables. We will calculate the mean, median and standard deviations for quantitative variables, and the absolute and relative frequency for qualitative variables.

The 95 % confidence interval will be applied. The analysis will be made following an intention-to-treat procedure. The baseline comparison will be made between the main variables that we expected to be related to the primary outcome using the Chi-Square test or an analysis of variance (ANOVA).

The between-group comparison for the primary outcome will be explored using the Chi-Square Test. The Relative Risk Reduction (RRR), the Absolute Risk Reduction (ARR) and the Number Needed to Treat (NNT) will be calculated. Inferences for the secondary outcomes will be made using an ANOVA or Chi-Square test. Each group will be analyzed separately. The comparison using PPS groups is unreliable because of the presence of unknown and uncontrolled confounders. It is necessary to make a comparison between RCT groups alone and analyses which include the PPS groups should be treated as observational studies with known confounding factors adjusted for in the analysis. Then the analysis will be performed following the next steps:

Comparison in RCT group: this will be made between each intervention arm versus control arm (intervA versus control; intervB versus control) and between intervention A and intervention B.

Comparison between RCT and PPS groups: this will be performed between the intervention arms of each group (intervA RCT group versus intervA PPS group; intervB RCT group versus intervB PPS group).

Finally, a logistic regression model will be performed for the primary outcome (performance of correct inhalation technique (yes/no)), considering the intervention as the predictive variable and the rest of the independent measures as the possible modifying factors. We will use the usual 5 % significance level (α = 0.05) and the SPSS statistical package, version 15.0, to run the proposed analysis.

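### Correction of critical mistakes is described for the control arm but not for leaflet arm A, so A versus control, followed as written, does not isolate the leaflet

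*Protocol article*

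**What the plan says.** The article describes what happens in each randomised arm when technique is assessed.

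- **Control** (Recruitment, last paragraph). At inclusion the patient's technique is tested and mistakes are recorded. Then: "The interviewer will only correct the critical mistakes". At follow-up, mistakes are recorded only, and the Follow-up section lists only measurement for this arm.
- **Arm A** (Intervention, written information). Mistakes are recorded, and then "the interviewer will give the leaflet to the patients and will invite them to read it and to identify differences" between the leaflet and their own technique. At follow-up they are asked about the leaflet and what they found. The Follow-up section adds encouragement with the leaflet at all four visits. No section mentions correction by the interviewer.
- **Arm B** (Intervention, leaflet plus training). The trainer demonstrates, the patient practises, and mistakes are explicitly corrected at follow-up.

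Statistical analysis makes A versus control one of three comparisons within the randomised group. The primary outcome is correct technique, yes or no, with relative and absolute risk reduction and number needed to treat. On size, the Sample size section says: "This was calculated to detect a correct inhalation technique percentage difference between groups of 25" percent, "with a statistical power of 80 % and a confidence level of 95" percent, "assuming a percentage of expected losses of 40" percent. It gives no control rate.

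**The concern.** An implementer who follows the text would correct critical mistakes in control and train fully in B, but would correct nothing in A. Control would then hold a teaching element that A lacks, and one that acts directly on the primary outcome. The authors' own Background suggests why this could matter: "Written instruction alone is insufficient in teaching correct inhalation techniques", and it calls verbal instruction with assessment essential.

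Two things are at stake. The first is interpretation: a null or reversed A-versus-control result could not be read as failure of the leaflet, and a number needed to treat would be relative to a comparator whose content is not named in the objective. The second is the planned difference. The only rate of correct technique before instruction is about 25%, from the statement that "we observed that up to 75 % of patients do not perform a correct inhalation technique". That rate was observed before any correction. If correction raises the control rate and A receives none, the gap between the two narrows.

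**Working it through.** **1. The arms side by side, as written**

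| | Control | Arm A | Arm B |
|---|---|---|---|
| Inclusion: mistakes recorded | yes | yes | technique demonstrated to the instructor |
| Inclusion: correction in person | critical mistakes | not mentioned | full training |
| Inclusion: leaflet | no | yes | yes |
| Follow-up: correction in person | not mentioned | not mentioned | yes |
| Follow-up: encouragement with leaflet | no | all four visits | yes |

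A and control therefore differ in two respects that pull in opposite directions: leaflet with encouragement (A only) and one limited correction (control only, as written). The A-minus-control difference mixes the two.

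**2. Reproducing the planned size**

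Inputs: difference 25 points, power 80%, confidence 95%, losses 40% (Sample size); α = 0.05 (Statistical analysis); 99 per arm (Discussion). Assumptions: two-sided test; control rate 25% (100% − 75%, Background), hence 50% under intervention.

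n = [z₀.₉₇₅·√(2p̄q̄) + z₀.₈₀·√(p₁q₁ + p₂q₂)]² / d², with p̄ = 0.375 and d = 0.25:

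- √(2 × 0.375 × 0.625) = 0.6847 and √(0.1875 + 0.25) = 0.6614
- n = (1.960 × 0.6847 + 0.8416 × 0.6614)² / 0.0625 = 57.7, so 58; 58/0.6 = 96.7, so 97

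With the pooled variance in both terms: n = (1.960 + 0.8416)² × 0.46875 / 0.0625 = 58.9, so 59; 59/0.6 = 98.3, so 99. This is the stated figure. The same arithmetic also fits 50% versus 75%, so the article does not fix which control rate was used. After 40% losses, 99 × 0.6 = 59.4, or about 59 evaluable per arm.

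**3. Illustration: control lifted by correction, A unchanged at 50%**

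Power ≈ Φ{[d√n − 1.960·√(2p̄q̄)] / √(p₁q₁ + p₂q₂)}. For a control rate of 30% with n = 59: (0.20 × 7.681 − 1.960 × 0.6928) / 0.6782 = 0.263, and Φ(0.263) = 0.60. Exact enumeration of the uncorrected chi-square test gives 0.61.

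| Control rate (assumed) | Gap | 59 per arm: formula | 59 per arm: exact | 99 per arm: formula |
|---|---|---|---|---|
| 25% | 25 | 81% | 81% | 96% |
| 30% | 20 | 60% | 61% | 82% |
| 35% | 15 | 38% | 38% | 57% |
| 40% | 10 | 19% | 20% | 29% |

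**4. Counter-check: the same lift in both arms**

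If A patients receive the same correction and both rates rise equally, the gap stays at 25 points. Exact power with 59 per arm is then 79% to 81% for control rates of 25% to 40%. The loss in step 3 arises only if the arms are treated differently.

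**The case against.** The strongest reply is that arm A's text is silent; it does not exclude correction. The article is condensed and refers to a researchers' manual that may settle the matter. The control sentence can also be read as a ceiling on what controls receive, not as something unique to them. This stands: a reader might infer that A patients are denied correction, but the documents do not say so. What remains is that correction is spelled out for control and for B and appears nowhere for A.

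A second reply is that control correction is described at inclusion only, while A has contact and encouragement at every follow-up visit, so the correction may fade over 12 months. This also stands, and it rules out describing the contrast simply as leaflet versus verbal teaching.

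Third, a reader might infer that the plan treats control as no education. No section does; the arm is called control and its correction is openly stated. Nor does the Background remark on written instruction show that one limited correction beats a leaflet with repeated encouragement.

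Fourth, the power loss is not established. The lift is assumed, 75% is an upper figure, and repairing only critical mistakes need not make a patient correct if every step must be right. With no losses, power at a control rate of 30% would still be 82%. The illustration concerns A versus control, not the fully trained arm B.

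Finally, a control with minimal correction is a legitimate choice, and a bias towards no difference leaves a positive result for A credible. That is fair, provided the comparator is named.

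**Conclusion.** The point holds in a limited form. As written, A versus control compares a leaflet with repeated encouragement against a single limited correction of critical mistakes. It does not isolate the leaflet, and it is biased towards no difference if that correction works.

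This is a cheap improvement to a main randomised comparison, not a fault that invalidates the trial. The sample size arithmetic is sound under 25% versus 50%. A reader might infer that the trial is underpowered, but the documents do not support that: the fall from 81% to about 61% or 38% rests on an assumed control rate of 30% or 35%, on A staying at 50% and on the full 40% losses. It shows only that the design has little slack.

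**What to change.** 1. Reconcile the Recruitment, Intervention and Follow-up sections so that they state whether critical mistakes are corrected in arm A, at inclusion and at follow-up, and handle critical mistakes in the same way in control and arm A. Which rule applies is the sponsor's decision.
2. Record each correction given, by arm and visit, on the existing mistakes template.
3. If the difference between arms is deliberate, name the comparator in the objective and conclusion as control with correction of critical mistakes, and interpret A versus control accordingly.
4. State the control rate assumed in the sample size.

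The cost is small changes to protocol and manual wording and one extra entry on the template. The stated effect of A against control may turn out less favourable.

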### Follow-up

All study groups will undergo the same follow up: five visits during one year

#### Control group

Visit one will take place one month after the inclusion visit. Primary and secondary outcomes will be measured (excluding spirometry and quality of life).

Visit two will take place three months after the inclusion visit. All the study data will be recorded.

Visit three will take place six months after the inclusion visit. Primary and secondary outcomes will be measured (excluding spirometry and quality of life).

Visit four will take place 12 months after the inclusion visit. All the study data will be recorded.

#### Intervention A group

Visit one will take place one month after the inclusion visit. Primary and secondary outcomes will be measured (excluding spirometry and quality of life) and correct inhalation techniques using the designed leaflet will be encouraged.

Visit two will take place three months after the inclusion visit. All the study data will be recorded and correct inhalation techniques using the designed leaflet will be encouraged.

Visit three will take place six months after the inclusion visit. Primary and secondary outcomes will be measured (excluding spirometry and quality of life) and correct inhalation techniques using the designed leaflet will be encouraged.

Visit four will take place 12 months after the inclusion visit. All the study data will be recorded and correct inhalation techniques using the designed leaflet will be encouraged.

#### Intervention B group

Visit one will take place one month after the inclusion visit. Primary and secondary outcomes will be measured (excluding spirometry and quality of life), correct inhalation techniques using the leaflet will be encouraged and training by the monitor will focus on motivational aspects.

Visit two will take place three months after the inclusion visit. All the study data will be recorded and correct inhalation techniques (using both the leaflet and the training) will be encouraged.

Visit three will take place six months after the inclusion visit. Primary and secondary outcomes will be measured (excluding spirometry and quality of life) and correct inhalation techniques using the leaflet will be encouraged and training by the monitor will focus on motivational aspects.

Visit four will take place 12 months after the inclusion visit. All the study data will be recorded, correct inhalation techniques using the leaflet will be encouraged and the training with the monitor will focus on motivational aspects.

### Statistical analysis

A descriptive statistical analysis will be performed for all the study variables. We will calculate the mean, median and standard deviations for quantitative variables, and the absolute and relative frequency for qualitative variables.

The 95 % confidence interval will be applied. The analysis will be made following an intention-to-treat procedure. The baseline comparison will be made between the main variables that we expected to be related to the primary outcome using the Chi-Square test or an analysis of variance (ANOVA).

The between-group comparison for the primary outcome will be explored using the Chi-Square Test. The Relative Risk Reduction (RRR), the Absolute Risk Reduction (ARR) and the Number Needed to Treat (NNT) will be calculated. Inferences for the secondary outcomes will be made using an ANOVA or Chi-Square test. Each group will be analyzed separately. The comparison using PPS groups is unreliable because of the presence of unknown and uncontrolled confounders. It is necessary to make a comparison between RCT groups alone and analyses which include the PPS groups should be treated as observational studies with known confounding factors adjusted for in the analysis. Then the analysis will be performed following the next steps:

Comparison in RCT group: this will be made between each intervention arm versus control arm (intervA versus control; intervB versus control) and between intervention A and intervention B.

Comparison between RCT and PPS groups: this will be performed between the intervention arms of each group (intervA RCT group versus intervA PPS group; intervB RCT group versus intervB PPS group).

Finally, a logistic regression model will be performed for the primary outcome (performance of correct inhalation technique (yes/no)), considering the intervention as the predictive variable and the rest of the independent measures as the possible modifying factors. We will use the usual 5 % significance level (α = 0.05) and the SPSS statistical package, version 15.0, to run the proposed analysis.

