#### Independent variables

Independent variables will be: age, sex, educational level, comorbidity, smoking history, COPD severity grade (according to SEPAR guidelines [28]), prescribed medication, family support (Family Apgar Test [29]): and social support (DUKE-UNC Test [30]).

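### The planned tests in the randomized arms are valid but make no use of baseline technique or baseline secondary values, so some precision from data already collected is lost

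*Protocol article*

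**What the plan says.** All references are to the protocol article.

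- Statistical analysis, primary outcome: "The between-group comparison for the primary outcome will be explored using the Chi-Square Test". Relative and absolute risk reduction and the NNT follow, with no adjustment mentioned.
- Statistical analysis, secondary outcomes: "Inferences for the secondary outcomes will be made using an ANOVA or Chi-Square test".
- Statistical analysis, final model: a logistic regression for correct technique (yes/no), "considering the intervention as the predictive variable and the rest of the independent measures as the possible modifying factors".
- Independent variables: "Independent variables will be: age, sex, educational level, comorbidity, smoking history, COPD severity grade", then prescribed medication, family support and social support. Neither baseline technique nor the baseline value of any secondary outcome is listed.
- Recruitment: once patients are randomized, all study data are recorded and "the performance of correct inhalation techniques will be measured in all groups (inclusion visit").
- The one stated use of baseline data is a check of group comparability: "The baseline comparison will be made between the main variables that we expected to be related to the primary outcome", by chi-square or ANOVA.
- The same section says that analyses including the preference arms must adjust for known confounders.

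**The concern.** Nothing in the inclusion criteria restricts entry to patients with faulty technique. The Background and the Discussion put incorrect use at up to 75 %, so roughly a quarter or more may already be correct on entry. If baseline technique predicts later technique, a test that ignores it leaves explainable variation in the error term. It also carries any chance imbalance at entry into the risk difference and the NNT. Comparing the arms at baseline can reveal such an imbalance but does not remove it. The same holds for spirometry, dyspnea and quality of life, which are measured at entry and then analyzed without their entry values.

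In the comparisons of randomized with preference arms there is no randomization to fall back on. Existing skill could plausibly influence whether a patient chooses the leaflet or the training, yet it is not among the listed covariates.

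**Working it through.** **Inputs.** From Sample size: "This was calculated to detect a correct inhalation technique percentage difference between groups of 25" percentage points; the power is set at 80 %, the confidence level at 95 % and the expected losses at 40 %. From the Discussion: 99 patients per arm. Assumed: two-sided α = 0.05 and a control rate of 25 % (the complement of the 75 % incorrect), since the article states neither a control rate for the calculation nor the sidedness. Also assumed: the correlation ρ between baseline and follow-up technique, taken from 0 to 0.5.

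**1. The plan's own figure.** With 25 % versus 50 %, the pooled proportion is 0.375 and

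n = [1.96·√(2·0.375·0.625) + 0.8416·√(0.25·0.75 + 0.5·0.5)]² / 0.25² = (1.3419 + 0.5567)² / 0.0625 = 57.7, so 58 per arm.

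58 / (1 − 0.40) = 96.7, so 97 per arm against 99 stated. The figure reproduces to within two patients.

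**2. Power of the unadjusted chi-square.** 99 × 0.60 = 59.4, so 59 completers per arm.

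Power = Φ[(0.25·√59 − 1.3419) / 0.6614] = Φ(0.874) = 0.81.

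**3. Power after adjustment.** Adjustment multiplies the variance by about 1 − ρ², so the effective n per arm is 59 / (1 − ρ²), entered in the formula of step 2. The simulation column gives a test stratified on baseline technique (Mantel-Haenszel, 40,000 trials). In the same trials the chi-square stayed at about 0.81.

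| ρ | Variance reduction | Effective n | Power, formula | Power, simulation | Completers needed per arm for 80 % |
|---|---|---|---|---|---|
| 0 | 0 % | 59.0 | 0.809 | 0.808 | 58 |
| 0.2 | 4 % | 61.5 | 0.825 | 0.823 | 56 |
| 0.3 | 9 % | 64.8 | 0.845 | 0.842 | 53 |
| 0.4 | 16 % | 70.2 | 0.873 | 0.874 | 49 |
| 0.5 | 25 % | 78.7 | 0.907 | 0.911 | 44 |

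With 25 % correct at baseline and 50 % at follow-up, ρ cannot exceed √[(0.25·0.50)/(0.75·0.50)] = 0.58.

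**4. Chance imbalance at entry.** With 25 % correct at baseline, the standard deviation of the difference between two arms is √(2·0.25·0.75/59) = 0.080, or 8 percentage points among completers (6 points with 99 per arm).

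**5. Continuous secondary outcomes.** ANCOVA on the baseline value has variance 1 − r² relative to ANOVA: 25 % lower at r = 0.5 and 49 % lower at r = 0.7. Both values of r are illustrations, not figures from the article.

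**The case against.** Four arguments carry weight.

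- *The tests are sound.* In the randomized arms an unadjusted chi-square with absolute risk reduction and NNT is valid, and step 2 shows that it meets the planned power. This stands. A reader might infer that the primary analysis is biased or that the trial is underpowered; the article supports neither.
- *The gain is undocumented.* No baseline/follow-up association is reported, so one cannot claim that baseline technique is a dominant predictor. The design may weaken it: control patients have critical mistakes corrected at inclusion, and patients in intervention B practise until correct or tired. The Discussion reports incorrect use falling from 75 % to 17 % in an earlier program. With 25 % correct before and 83 % after, ρ cannot exceed √[(0.25·0.17)/(0.75·0.83)] = 0.26. This stands, and it is why the size is given as a range that includes zero.
- *Baseline is scored after randomization.* No blinding of the scorer is described. Suppose there is no true effect, 25 % are correct, and baseline is scored 10 points too low in one arm only. A baseline-stratified test then has a type I error of about 6 to 7 % at a baseline/follow-up odds ratio of 4.5 and about 10 % at 12, while the chi-square stays near 5 %. These settings are assumptions, but the risk is real. It limits the remedy without defeating it: in intervention A technique is performed before the leaflet is given, in B it is demonstrated before training, and in controls mistakes are noted on a template.
- *An unseen analysis plan may cover it.* The article names the tests and lists the independent variables, so the point concerns stated choices and not omitted detail. The final logistic model does adjust for other variables, but not for this one.

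**Conclusion.** The point holds as a missed gain in precision. Under 25 % versus 50 % correct with 59 completers per arm, adjustment adds about 1 to 4 points of power at a correlation of 0.2 to 0.3, about 6 at 0.4, about 10 at 0.5 and none at 0. The control rate, the sidedness and the correlation are assumptions. The planned tests in the randomized arms remain valid and adequately powered on the plan's own terms. For the comparisons with the preference arms the omission matters more in kind, because the article itself asks for adjustment for known confounders there; its size cannot be computed from the article.

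**What to change.** - In the randomized arms, make the primary comparison a logistic regression on arm and baseline technique (yes/no). Report a standardized risk difference with its 95 % CI and derive the NNT from it.
- Keep the unadjusted chi-square as a sensitivity analysis. If knowledge of the arm could have affected baseline scoring, show both results side by side.
- Use ANCOVA on the baseline value for the continuous secondary outcomes.
- Add baseline technique to the covariates of the final logistic model and of the comparisons between randomized and preference arms.
- State that the baseline score is recorded before any leaflet, training or correction and, for patients still to be enrolled, preferably before allocation.

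Cost: no new variable is needed, and the analysis part is a change of wording to be fixed before the data are analyzed. The last item is a small procedural change at the inclusion visit. Scoring before allocation cannot be applied retrospectively to patients already enrolled, since recruitment has been active since 2010.
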